### Intervention

#### Participatory Design

The start of the study was preceded by a 6-month participatory phase to recruit relevant stakeholders from the city of Duesseldorf to a stakeholder advisory board supporting the research team in the development and implementation of the intervention. Relevant stakeholders include representatives of the involved local communities, the public health service, the city of Duesseldorf’s administrative offices for sports and social services, 2 statutory health insurances, and the city’s Chamber of Industry and Commerce (*Industrie und Handelskammer*), as well as several companies, the physician’s chamber, and the city’s soccer club. These stakeholders were invited to participate in the board during the first 2 months of the participatory development phase. In months 3 to 6 of this phase, monthly meetings were held to adapt the Ghent intervention to the Duesseldorf context and develop a joint strategy for implementing the intervention. During these meetings, ideas concerning intervention activities and the steps necessary for implementation were brainstormed and continuously prioritized. The meetings will be continued during the implementation phase of the intervention.

#### Intervention Components

The complex intervention “10,000 Steps Düsseldorf” is a universal prevention approach aimed at motivating residents of the intervention districts of Duesseldorf to be more physically active in everyday life. The intervention components are described in further detail in the subsequent sections. In addition, Table 3 compares intervention content of “10,000 Steps Duesseldorf” to the preceding interventions in Ghent and Rockhampton.

**Table 3 table3:** Socioecological intervention components and dissemination strategies of “10,000 Steps” studies (adapted based on Van Acker et al [51]).

	10,000 Steps Rockhampton (2-year project)	10,000 Steps Ghent (1-year pilot)	10,000 steps in Flanders	10,000 Steps Duesseldorf
Intrapersonal	Sale (GP^a^ and health services) and loan (libraries and video shops) of pedometers Website of “10,000 Steps Rockhampton”	Sale (local town shop, and health services) and loan (sport service) of pedometers Website of “10,000 Steps Ghent”	Sale and loan of pedometers in every municipality (local public services) Website updated from “10,000 Steps Ghent”	Website of 10,000 steps in Duesseldorf Provide recommendations for step counters and PA^b^ trackers on the website of “10,000 Steps Düsseldorf”
Interpersonal	Promotion of PA by health professionals and print media	Promotion of PA and distribution of folders through GPs, dietitians, physical therapists, and schools; posters in public places	Promotion of PA and distribution of folders and posters in public places Personalized contact with citizens (eg, personalized letter, mail, or phone)	Promotion of PA via step-count competitions with family and friends
Organizational	Community events and specific projects for GPs, for health services involvement, and for workplaces	Community events and specific projects for workplaces and for groups of older people	Community events and projects for the entire population and all domains of active living (PA for transport, at work, in the household, and during leisure time)	Community events and specific projects for workplaces (step-count competitions) and for groups of older people
Community	Local mass media campaign 10,000 Steps a Day—Every Step Counts Environmental: street signs, distribution of maps, and promotion of dog walking	Local media campaign 10,000 Steps a Day—Every Step Counts, 30 minutes MVPA^c^ guideline Environmental: street signs, walking circuits and billboards	Local mass media campaign in every municipality 10,000 Steps a Day—Every Step Counts, 30 minutes MVPA guideline Environmental: street signs and walking circuits	Local mass media campaign 10,000 Steps per Day—Every Step Counts Environmental: street signs and distribution of maps
Policy	Partnerships between local government and key members of community organizations, some with high-level experience in PA promotion Sale and loan of pedometers	Partnerships between the local city and provincial government, health insurance companies, and the local health promotion service Sale and loan of pedometers	Partnerships between the adopting organization and a minimum of 1 (other) local government service or 2 professional organizations Sale and loan of pedometers	Partnerships between local government and key members of community and professional organizations, health insurance companies, and commercial organizations targeting PA (eg, local soccer clubs)
Strategies for dissemination among potential adopters	Local: recruitment of community partners by researchers (microgrants) to form a local PA task force and GP training	Local: recruitment of community partners by researchers to form a local steering committee	Regional: website, mailing of the project manual and pilot study results, group meetings, displays at conferences, and e-articles	Local: recruitment of community partners by researchers to form a local steering committee; a website and e-mailing of invitations to participate, including a checklist for intervention implementation

^a^GP: general practitioner.

^b^PA: physical activity.

^c^MVPA: moderate to vigorous physical activity.

#### Intrapersonal Level: “10,000 Steps Duesseldorf” Website

The website was jointly developed with a marketing company and is based on the content of the website of the Flemish Institute of Healthy Living and Ghent University [52]. The content of the website is based on several behavior change techniques (eg, goal setting [behavior], discrepancy between current behavior and goal standard, self-monitoring of behavior, and social comparison [53]). It contains the WHO recommendations for PA and information on why and how to increase the personal daily step count, including health benefits. The target groups are individuals, groups (circles of friends and acquaintances), and organizations (eg, companies). In line with the main intervention message “Every Step Counts,” tips and information are provided on how to integrate more steps into everyday life. There are also recommendations for steps counters and PA trackers and a calendar indicating current events and offers regarding PA in the city of Duesseldorf. Visitors can create a personal profile to monitor steps, receive weekly and monthly overviews of steps, upload photos, convert other activities to steps (eg, bicycling or swimming), compare and exchange ideas with other intervention participants, and participate in step-count competitions. Information on the ongoing study examining the effects of the intervention is also included, along with references to previous projects in Ghent and Rockhampton.

#### Interpersonal Level: Promotion of PA in Groups

In step-count competitions with family and friends organized via the website, individuals are encouraged to monitor their steps, set goals, and motivate each other to engage in PA. The step-count competitions will take place as events in the entire city or in selected city districts. Step-count competitions will also take place in companies.

#### Organizational Level: Specific Projects for the Workplace and for Groups of Older People

Step-count competitions organized via the website will be advertised and implemented in companies and other organizations located in the intervention districts. Members of the stakeholder advisory board will help publicize the program and its website via email lists of companies, general practitioners, senior citizen clubs, sports clubs, and health insurance offices and by using their social media channels. In addition, print materials describing the aim and content of the intervention (brochures, flyers, and stickers), which were developed based on the print materials of 10,000 Stappen will be made available to organizations.

#### Community Level: Community Events, Local Mass Media Campaign, Environmental Street Signs, and Walking Circuits

A range of community events focusing on PA promotion are foreseen, such as the ascent of the Duesseldorf television tower (*Skyrun*), a family event in the local soccer stadium with representatives of the soccer team, and city rallies with different local themes coming from arts, culture, and history. In addition, the project will be linked to existing events, such as events organized by Duesseldorf’s administrative office for sports, city marathons, and events for health promotion organized by other entities. These events will be publicized via press releases and via the website’s social media channels and the members of the stakeholder advisory boards’ social media channels. The main intervention message, “Every Step Counts,” will be disseminated via various media channels and in public places. The aim of the media campaign is to encourage participation, as well as linking up with existing events in Duesseldorf. Flyers, as well as stickers and brochures, will be provided at the events.

In addition, for each intervention district, routes have been developed that support residents in reaching 10,000 steps per day. There is a range of 30- to 60-minute routes that can be easily integrated into everyday life and reflect the guiding principle of the project. In this context, the project’s own “Komoot” account (Komoot is an app to plan routes and socially network regarding outdoor activities) was created, on which suitable tours will be shared, which can also be shared on the website. The tours fulfill various criteria (eg, good lighting, security, accessibility, availability of seating and public toilets, and general attractiveness). Signage with routes, including information on the number of steps, and QR codes to the website will be posted in parks and public spaces of the intervention districts.

### Process Evaluation

The aim of the process evaluation is to document the frequency and intensity of the implemented intervention activities at every level of the complex intervention over the course of 1 year. This ensures intervention fidelity, meaning that it will be possible to assess whether the implementation of the intervention in Duesseldorf, Germany, was comparable with the implementation of the original intervention in Ghent. According to the RE-AIM framework [54], reach (the extent to which the program reaches the intended target group), effectiveness, adoption, implementation, and maintenance (of individual behavior change of the target group as well as long-term decision-making behavior of relevant stakeholders to consolidate intervention activities) will be assessed. A similar approach will be followed as developed by Van Acker et al [51].

For this study, the five components of the framework will be determined based on various data sources: (1) the commercial register of companies located in the intervention districts or the register of the Chamber of Commerce and Industry, (2) the individual-level data assessed in the telephone-administered interviews, and (3) a web-based questionnaire that heads of participating organizations (eg, companies) will be invited to participate in. The web-based questionnaire includes four thematic item blocks regarding (1) the characteristics of the respective organization (eg, company size) and knowledge of the intervention, (2) the adoption of the intervention and reasons for or against adoption, (3) the implementation of the intervention (eg, of the different intervention components, frequency and duration, and resources needed to implement the intervention or raise awareness), and (4) long-term intervention maintenance (reasons for or against it). Examples of the items in the web-based survey are shown in Textbox 1.

To estimate reach, first, the number of organizations potentially participating in the program in each intervention district will be determined based on the commercial register or by the Chamber of Commerce and Industry. Second, the number of organizations participating in the program will be assessed and surveyed using the web-based questionnaire. Furthermore, the proportion of individuals who were aware of intervention activities will be calculated, and to determine representativeness, age, gender, level of education, and occupation of those aware of the intervention will be compared with those unaware of the intervention. Effectiveness will be determined by comparing the 4 domains of active living (PA for transport, to work, in the household, and during leisure time activities) among individuals with and without awareness of the intervention. Adoption will be determined by estimating the proportion and representativeness of organizations implementing the intervention (compared with those not implementing the intervention). The implementation of the different intervention components (website, print-based materials, and initiation of partnerships) will be assessed, and an implementation score ranging from 0 to 100 will be calculated (see the study by Van Acker et al [51] for more details regarding the calculation of the score). To estimate maintenance, the proportion of organizations that voiced the intention to maintain the intervention will be determined.

Example items of the web-based questionnaire used in the process evaluation.

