Is the intervention “10,000 Steps Ghent” adaptable and transferrable to the context of city districts in the state of North Rhine-Westphalia?Is the intervention “10,000 Steps Duesseldorf” effective for the promotion of PA among residents of the districts involved?Do individuals located in the city that the intervention is implemented in (Duesseldorf) engage in more PA compared with individuals located in the control city (Wuppertal) after 1 year? Does the absolute number of steps taken per week increase more for individuals residing in the intervention city than in the control city?Does the proportion of those achieving the PA goal of 10,000 steps increase more in the intervention than in the control city after 1 year of potentially being able to participate in intervention activities?To what extent can these differences be attributed to the adoption, implementation, and maintenance of the intervention in the intervention city compared with the control city?What are the costs associated with the provision of the intervention? Does the intervention affect health care use and indirect costs? Is the intervention cost-effective in terms of additional costs per additional person who achieves the PA goal of 10,000 steps and additional costs per additional quality-adjusted life year (QALY) gained compared between the intervention and control cities after 1 year of potentially being able to participate in intervention activities?

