	**GPAQ^f^** **[32]**			
		Intensive PA during paid and unpaid work	T_0_, T_1_	
		Days of intensive PA in a usual week at work	T_0_, T_1_	
		Time of intensive PA on such a day at work	T_0_, T_1_	
		Moderate PA at work	T_0_, T_1_	
		Days of moderate PA in a usual week at work	T_0_, T_1_	
		Time of moderate PA on such a day at work	T_0_, T_1_	
		Locomotion by foot or bicycle	T_0_, T_1_	
		Days in a usual week getting around from one place to another by foot or bicycle	T_0_, T_1_	
		Time invests to get from one place to another by foot or bike	T_0_, T_1_	
		Intensive PA during leisure time	T_0_, T_1_	
		Days of intensive PA in a usual week during leisure time	T_0_, T_1_	
		Time of intensive PA in a usual week during leisure time	T_0_, T_1_	
		Moderate PA during leisure time	T_0_, T_1_	
		Days of moderate PA in a usual week during leisure time	T_0_, T_1_	
		Time of moderate PA in a usual week during leisure time	T_0_, T_1_	
		Time of sedentary behavior on a usual day	T_0_, T_1_	
		Changes of PA in the past year in general	T_0_, T_1_	

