**Perception and use of the intervention^h^**				
	**Self-generated items**			
		Awareness of the intervention, use of various intervention components	T_1_	

^a^PA: physical activity.

^b^GEDA: Gesundheit in Deutschland aktuell.

^c^Baseline assessment.

^d^Follow-up assessment.

^e^SF-1: Short Form-1.

^f^SOEP: Sozio-oekonomisches Panel.

^g^ICECAP-A: The ICEpop CAPability measure for adults.

^h^Only assessed in the intervention group.

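### RE-AIM effectiveness is defined as aware versus unaware residents, a self-selected contrast within the intervention city with no stated adjustment, and one of its four activity domains cannot be derived from the listed GPAQ items

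*Protocol article*

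**What the plan says.** The Process Evaluation section of the protocol article fixes the definition: "Effectiveness will be determined by comparing the 4 domains of active living (PA for transport, to work, in the household, and during leisure time activities", and the comparison is made "during leisure time activities) among individuals with and without awareness of the intervention". Its individual-level data come from the telephone interviews.

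Table 2 lists the relevant item as "Awareness of the intervention, use of various intervention components", at T1 only, with the footnote "Only assessed in the intervention group".

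Under reach, the same section plans to describe how the two groups differ: "age, gender, level of education, and occupation of those aware of the intervention will be compared with those unaware of the intervention". That comparison serves representativeness. It is not carried into the effectiveness contrast.

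The Statistical Analyses section describes matching weights from a propensity score model, for the primary outcome compared between intervention yes and no.

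Table 1 lists the GPAQ at T0 and T1. Its vigorous work item is "Intensive PA during paid and unpaid work", its transport item is "Locomotion by foot or bicycle", and it has leisure-time and sedentary items.

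**The concern.** Awareness arises after baseline and by the resident's own behaviour. Much of the programme is met through route signs in parks, sports clubs, city marathons and a step-tracking website, so residents who were already active may be more likely to notice it. A difference between aware and unaware residents may then exist without any effect of the programme. Because the control city has no awareness data, the contrast has no counterpart there against which to judge it.

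At stake is a result reported under the label of effectiveness in the process evaluation that mixes effect with selection, and a planned four-domain table of which one row has no listed source.

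**Working it through.** The article gives no figure for this contrast, so there is nothing to reproduce. The check compares the relevant sections and then shows why the bias cannot be sized.

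**1. The contrast against the measurement plan**

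| Feature | Where stated | Consequence |
|---|---|---|
| Aware versus unaware | Process Evaluation | Groups formed by the residents themselves |
| Awareness at T1 only | Table 2 | Group membership is post-baseline |
| Intervention group only | Table 2, footnote h | Contrast exists only within Duesseldorf |
| Weights for intervention yes versus no | Statistical Analyses | Do not cover awareness as written |
| Demographics of aware and unaware compared | Process Evaluation, reach | Descriptive, no adjustment stated |
| GPAQ at T0 and T1 | Table 1 | Baseline activity is available for adjustment |

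**2. Direction of the bias under no effect**

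Let aware and unaware residents differ at T0 by g, let the T0–T1 correlation be r with equal SDs, let selection act only through measured T0 activity, and let the programme do nothing. The expected aware-minus-unaware difference is then:

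- T1 values only: r × g
- change from T0: r × g − g = −(1 − r) × g
- T1 adjusted for T0: 0

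For any g above 0 and r between 0 and 1, the first is positive, the second negative and the third zero. The article does not say which is planned.

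**3. An illustration on the step scale**

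This uses steps only because the article gives step figures. It gives no SD or correlation for any GPAQ domain.

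- Change intervals for the Ghent study, in the Introduction: 599 to 1192 (n=660) and −432 to 162 (n=634).
- SD of change = half-width / 1.96 × √n. This gives 296.5 / 1.96 × √660 ≈ 3886 and 297 / 1.96 × √634 ≈ 3815.
- With SD 4500 (Sample Size Calculation, stated there as an upper limit), r = 1 − SD_change² / (2 × 4500²). This gives 0.627 and 0.641, or about 0.634.
- Assume the odds of awareness rise 1.5-fold per SD of baseline activity. A simulation with no effect, at 30% and 50% awareness, gives a T1 gap of 1114 to 1124 steps, about 1119. The implied baseline gap is 1119 / 0.634 ≈ 1765 steps.
- T1 only: about +1119. Change: 1119 − 1765 ≈ −650. Adjusted for T0: about 0.

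For assumed odds ratios of 1.2, 1.3 and 2.0, the T1-only gap is about 520, 740 and 1800 steps. The odds ratios are assumptions throughout.

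**4. The four domains against the listed items**

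| Domain in Process Evaluation | GPAQ items in Table 1 |
|---|---|
| Transport | Yes, on foot or by bicycle |
| Work | Yes; the vigorous item pools paid and unpaid work |
| Household | No separate item |
| Leisure | Yes |

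Household activity can enter only as unpaid work, pooled with paid work. Pedometers and accelerometers give no domains. The wording of the work domain also differs: the Process Evaluation section speaks of activity to work, while Table 3 (Flanders column) has activity at work. Travel to work would overlap with transport.

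**The case against.** The strongest reply is that this is one component of an accompanying process evaluation. The trial's effectiveness questions are between-city and rest on the weighted comparison of pedometer steps. That is correct, and it sets the severity.

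A second reply is that an article may leave the model to a fuller plan, so silence on adjustment does not mean that none is intended. This stands in part: it rules out any claim about the size or sign of the bias. It does not remove the definition itself. The article fixes the contrast and the domains, and no adjustment is stated for them.

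Several stronger readings are tempting, and the documents do not support them:

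- *The analysis would show a favourable effect even if the programme did nothing.* This holds only for an unadjusted T1 comparison with selection towards active residents. A change score would point the other way.
- *The bias exceeds the 1000-step minimal relevant effect.* The outcome is GPAQ domains, not steps, and the awareness odds ratios are assumed.
- *The GPAQ cannot supply the domains.* It supplies three of four.
- *The definition contradicts the research question.* That question, "To what extent can these differences be attributed to the adoption, implementation, and maintenance of the intervention in the intervention city compared with the control" city, concerns adoption, implementation and maintenance, not the effectiveness component.
- *Contamination of controls is invisible.* Table 1 records the city each participant works in, so that route can be examined. Not asking Wuppertal residents about awareness is a limitation, not an error.

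**Conclusion.** The point holds and is minor. As defined, RE-AIM effectiveness is a self-selected, post-baseline contrast within the intervention city. No adjustment or weighting is stated for it, so it cannot separate effect from selection. The size and direction of the bias cannot be set from the documents, and the step figures above only show that the sign turns on the unstated model. Even a baseline-adjusted version would remain an association, because awareness may follow a change in activity during the year as well as precede it.

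The domain problem needs no assumption beyond reading Table 1 as the full list of activity items: three domains can be reported, a separate household domain cannot, and the work domain is worded in two ways.

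Nothing here touches the primary between-city comparison of steps.

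**What to change.** - Take RE-AIM effectiveness from the propensity-weighted between-city comparison of each GPAQ domain. The GPAQ is listed at T0 and T1 without restriction to one city.
- Keep aware versus unaware as a labelled association within Duesseldorf, adjusted for T0 activity in the same domain, T0 steps and demographics.
- Report three domains: work including unpaid and household work, transport, and leisure. Use one wording for the work domain. A household item added at T1 would have no baseline value, since baseline assessment ended in March 2022.
- Optionally, ask the awareness items in Wuppertal at T1 to gauge false recall and spill-over.

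The first three changes are wording and analysis of data already listed. The optional one adds a few questions to a planned telephone interview. Its drawback is that the control interview would mention the programme, so those items should come last.
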